### Surgical procedure

Depending on patient and surgeon preference, surgery will be performed laparoscopically or open. Ileocolic mesenteric mobilization and hemostatic division of the mesentery will be performed as reported [9]. In a conventional limited resection, the mesentery is resected within 3 cm from the bowel, leaving most of the mesentery in situ. In the extensive mesenteric resection group, a mesocolic resection is performed while avoiding the root region by dividing the mesentery 1 cm from the root of ileocolic artery and vein. The proximal mesenteric incision will be made just proximal to the mesenteric transition zone [9], while the distal incision will be placed where both the mesentery and intestine are macroscopically normal immediately distal to the region of disease. After resection, an ileocolic anastomosis will be then performed. The type of anastomosis construction and the anastomotic configuration are based on the individual surgeon’s preference.

We expect that the majority of patients should be treated with ileocolic resection and primary anastomosis. However, in selected cases the surgeon may elect to reroute the fecal stream away from an anastomosis with proximal stoma diversion based on the surgeons’ clinical judgment and intra-operative findings. The reasons for stoma diversion should be clearly documented. If a covering loop-ileostomy is fashioned then it is recommended that this be reversed (if feasible) after 3 months and that the time of ileocolic resection and ileostomy be considered as the starting point of postoperative surveillance. However, the date of reversal will also be recorded as it is possible that recurrence will differ in those patients who undergo diversion compared to those who are not.

### Postoperative examination of the resection specimen

The mesentery will be inspected and morphological features of mesenteric disease will be recorded. Mesenteric and mucosal disease scores will be documented [9]. For histopathological assessment, **e**ach specimen will be examined at two levels, intestinal and mesenteric. Each will be examined at a number of points along the longitudinal axis of the intestine [9].

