### Randomization

Given the nature of surgical procedures, it is not possible to blind the surgical team to the assigned treatment arm. However, patients will be blinded to the type of mesenteric excision performed. Eligible patients enrolled by each participating center will be randomized based on a computer-generated list maintained centrally. The randomization codes are uploaded on Google docs, and the study co-ordinator at each center will receive a link to the codes.. The group allocation will be conducted by a staff surgeon, or research assistant who is blind to the study by a sealed, opaque envelope. Individuals other than the surgical team involved in the trial will be blind to the assigned treatment arm according to the blinding guidelines indicated by Probst et al. [13].

After entering the abdomen, the surgeon will determine whether a hemostatic division of the mesentery is technically possible. If this is the case, as we would expect in the majority of patients, the envelope containing the randomization can be opened to find out what group the patient has been randomized to, and the operation proceeds as per the group allocation to either a mesenteric-based resection or conventional resection. If mesenteric division is not deemed possible, the patient will be excluded from the trial. The reasons for those that have not been randomized would be clearly reported. The number of excluded patient will be separately recorded. Alternatively, the patient may undergo initial stoma diversion followed by delayed resection with preoperative re-randomization in 6 months. This approach will be left to the discretion of the operating surgeon, while the reason for stoma creation should be documented. Patients undergoing delayed resection are, therefore, eligible for inclusion in the study.

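### Mesenteric scores taken from the specimen are not made comparable between arms, and the covariate rule does not keep them out of the adjusted analysis

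*Protocol article*

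**What the plan says.** Four statements in the protocol article bear on this.

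- **Timing of allocation (Randomization).** "After entering the abdomen, the surgeon will determine whether a hemostatic division of the mesentery is technically possible". If it is, "the envelope containing the randomization can be opened to find out what group the patient has been randomized to". Allocation is therefore revealed during the operation and before any tissue is removed.
- **Extent of resection (Surgical procedure).** In LME, "the mesentery is resected within 3 cm from the bowel, leaving most of the mesentery in situ". In EME, "a mesocolic resection is performed while avoiding the root region by dividing the mesentery 1 cm from the root of ileocolic artery and vein".
- **What is scored (Postoperative examination of the resection specimen).** Here the article sets out the macroscopic assessment as follows: "The mesentery will be inspected and morphological features of mesenteric disease will be recorded. Mesenteric and mucosal disease scores will be documented". Histology is also taken at an intestinal and a mesenteric level, at several points along the length of the bowel. The method is that of reference [9].
- **How variables reach the models (Statistical analysis).** Groups are compared with t tests, chi-square or Fisher's exact tests, and variables that differ significantly become covariates. The regression is a Cox model with forward conditional selection. Nothing confines the rule to variables measured before allocation.

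The End points section does not list the mesenteric score as a primary, secondary or 30-day outcome.

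**The concern.** A covariate used to adjust a randomised comparison should not itself be shaped by the treatment. The specimen-based mesenteric score is exposed to this on two counts. It is recorded after allocation, and the amount of tissue available to score is set by the arm. If scoring draws on mesentery beyond the strip next to the bowel, two patients with the same disease could receive different scores only because one was allocated to EME and the other to LME.

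While the score is only recorded and described, little follows. The stake comes from the covariate rule. A between-arm difference caused by the size of the specimen would look like an imbalance, would meet the criterion for adjustment, and could move the estimated effect of surgery on recurrence.

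**Working it through.** The plan gives no figure for this point, so there is none to reproduce. The check has three steps.

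**1. The sequence, set side by side**

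| Step | LME | EME |
|---|---|---|
| Mesentery assessed for divisibility | before allocation | before allocation |
| Envelope opened | during surgery | during surgery |
| Mesentery removed | within 3 cm of the bowel | to 1 cm from the root of the ileocolic vessels |
| Mesenteric score and histology | on that specimen | on that specimen |

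The score is post-allocation in both arms, and its tissue base differs by arm. The article states no common scoring zone and no score made before the envelope is opened.

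**2. How easily an artefact could trigger the covariate rule**

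Inputs: 116 patients (Sample size); 1:1 allocation (assumed, ratio not stated), so 116/2 = 58 per arm; two-sided 5% chi-square test (sidedness assumed). The score is treated as yes/no (assumed, since its format is not given). True severity is taken as equal in the two arms. The share scored positive is assumed to be p in EME, between 50% and 80%, and p − g in LME, where g is the purely artefactual gap.

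Chance of a significant result ≈ Φ[(g − 1.96 × SE0)/SE1], with m the mean of the two proportions, SE0 = √[2m(1 − m)/58] and SE1 = √{[p(1 − p) + (p − g)(1 − p + g)]/58}.

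Example, 60% against 40%: SE0 = √(0.50/58) = 0.0928; SE1 = √(0.48/58) = 0.0910; (0.20 − 0.182)/0.0910 = 0.198; Φ(0.198) = 0.58.

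| Assumed gap g | Chance of triggering the rule, p from 50% to 80% |
|---|---|
| 10 points | 19–24% |
| 20 points | 58–66% |
| 30 points | 91–93% |

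This is the chance of becoming a candidate covariate. Forward selection would keep the score only if it also predicts recurrence, which is when adjusting for it changes the treatment estimate.

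**3. Direction of the bias if the score is adjusted for**

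Suppose the operations have the same effect, recurrence is a with mesenteric disease and b without (a > b), and the LME specimen misses disease in a share g of patients.

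- Score-positive patients: rate a in both arms, so no difference.
- Score-negative patients: rate b in EME. In LME the rate is [g·a + (1 − p)·b]/(1 − p + g) = b + (a − b) × g/(1 − p + g).

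With p = 60% and g = 20 points, the false difference among score-negative patients is (a − b) × 20/60, one third of the prognostic gap. Over p = 50% to 80%, the fraction at g = 20 runs from 20/70 = 0.29 to 20/40 = 0.50. The unadjusted rates are equal, yet the adjusted comparison favours EME.

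**The case against.** The strongest reply is that the score has no analytic role. It is not an end point, an eligibility criterion, a Table 1 risk factor or a named covariate, and no subgroup analysis by mesenteric severity is described. The primary comparison by intention to treat does not need it. All of this stands, and it limits the point to a minor one. A reader drawn by the trial's mesenteric hypothesis might treat the score as a central biomarker; the document does not give it that standing.

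A reader might also infer that the score can never be obtained alike in the two arms. That is not supported. LME specimens do carry mesentery next to the bowel, histology is sampled along the length of the intestine, and the Discussion holds that mesenteric and mucosal changes develop together. The scoring method is in reference [9], which is not at hand, so it is unknown whether the score needs mesentery beyond that strip. What can be said is that the article does not make the score comparable.

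A third tempting inference is a breach of blinding, because the specimen may reveal the arm while "Individuals other than the surgical team involved in the trial will be blind to the assigned treatment arm". The article does not say who examines the specimen. If the surgical team does, it is already exempt. If a pathologist does, no listed end point depends on that assessment. No contradiction is established.

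It can further be said that scoring detail belongs in a fuller document and that the weakness lies in the covariate rule. The first is fair for the zone and the examiner. But the article does fix the specimen as the scored material, and no later analysis plan can recover a pre-allocation observation that was never made. The second is largely right, which is why the main repair is made to that rule.

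**Conclusion.** The point holds as a minor one. Mesenteric score and histology come from tissue whose extent is set by the allocated operation, and the covariate rule as worded would let a resulting difference into the adjusted efficacy analysis. The unadjusted intention-to-treat comparison is unaffected.

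The size is not known. The document gives no score distribution, so the gaps of 10 to 30 points, the 50–80% positive share, the yes/no format and 1:1 allocation are all assumptions. Under them the rule would be triggered in roughly one trial in five at the small end and nine in ten at the large end. Bias then follows only if the score is retained in the model. It would favour EME if higher scores go with more recurrence and LME specimens under-record disease. If the method of reference [9] uses only mesentery beside the bowel, the artefact could be small or absent.

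**What to change.** 1. In Statistical analysis, limit the covariate rule to variables measured before allocation, and state that specimen-derived mesenteric variables are descriptive only. Cost: one or two sentences.
2. In the specimen section, restrict any between-arm comparison of mesenteric score or histology to mesentery within 3 cm of the bowel, which is the zone both arms can provide. The Abstract describes LME as a close shave or less than 3 cm, so the width actually present should be noted. Cost: one sentence and one recorded measurement.
3. If mesenteric severity is wanted for baseline description, a subgroup or adjustment, record a simple in-situ grade at the existing intra-operative assessment, before the envelope is opened. Cost: one form field. That assessment now asks only whether the mesentery can be divided, so grading is a small added task.

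The downside of the third step is that an in-situ grade may be coarser than the specimen score of reference [9] and is not interchangeable with it. The two should be kept as separate variables.

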### Maintenance therapy

Prophylactic treatment is recommended after ileocolic intestinal resection in patients with at least one risk factor for recurrence (Table 1) [14]. For those developing endoscopic recurrence or clinical recurrence after surgery, management will be undertaken in keeping with local gastroenterology standard practice and guidelines.

**Table 1 Tab1:** Predictors of early postoperative recurrence after ileocolonic resection

Risk factor	Level of evidence
Smoking	EL1
Prior intestinal surgery	EL1
Penetrating disease at index surgery	EL2
Perianal location	EL2
Granulomata in resection specimen	EL2
Myenteric plexitis	EL3

### End points

In total, patients will be followed for 5 years after surgery. The primary end point of the study is postoperative surgical recurrence. Surgical recurrence is defined as the requirement for repeat surgery for a CD-related indication caused by recurrent disease in the same anatomical areas. If reoperation is required it should be documented whether the reason is a specific CD-related complication, or a complication related to surgery in general (i.e., hemorrhage, intraperitoneal collection not amenable to conservative treatment, wound dehiscence, anastomotic leakage). CD-related indications for surgery include: (1) development of symptoms refractory to medical treatment; and (2) development of a complication caused by CD (i.e., fistula, perforation, and obstruction).

Secondary end points include assessment of endoscopic recurrence and clinical recurrence. Endoscopic recurrence will be assessed using the widely accepted Rutgeert’s score [15]. Only disease (Rutgeert’s score i2, or higher) proximal to the anastomosis or in the perianastomotic area is considered to be consistent with endoscopic recurrence. Disease in other sites will not be considered to be recurrence. Clinical recurrence is defined as the presence of endoscopic disease or radiological evidence plus the presence of symptoms attributable to CD that are severe enough to require medical or surgical treatment.

In addition, intra-operative complications and 30-day postoperative outcomes will be evaluated. These include estimated blood loss, duration of surgery, postoperative morbidity, reoperation rate, and the length of postoperative hospital stay. Postoperative complications will be recorded and classified based on the Clavien-Dindo classification [16].

### Follow-up

Postoperative reviews will be conducted at 6-monthly intervals at which point patients will have a full clinical, endoscopic, and radiological assessment. The CD Activity Index [17] will be also recorded at each visit. If individuals experience symptoms suggestive of recurrent CD prior to the scheduled colonoscopy, they will undergo a colonoscopy and other investigations as deemed appropriate by their own gastroenterologist or surgeon to ascertain whether they have recurrent disease. If endoscopic or clinical recurrence are demonstrated, the patient should undergo continued follow-up if, or until, they develop recurrence requiring surgery. If patients do develop surgical recurrence, their participation in the study is terminated as they are considered to have reached the primary and ultimate end point.

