### Sample size

There are no registered or published randomized controlled trials (RCTs) comparing limited with extensive mesenteric resection in patients with CD. Our sample size calculation is based on the surgical recurrence in a retrospective study reported by Coffey et al. [9]. It is estimated that 30% of subjects undergoing an ileocolonic anastomosis with conventional limited mesenteric excision would develop surgical recurrence at 60 months after surgery. To detect a 20% decrease in the surgical recurrence rate after wide mesenteric excision with 80% power and 5% significance, a total of 100 patients must be recruited. The sample size is adjusted to 116 to allow for a 10% loss to follow-up and 5% anastomotic leak.

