### Statistical analysis

Data will be presented as median (range), mean, and standard deviation for continuous variables, and percentages for categorical and ordinal data. In order to test whether there are differences between the two groups in the reduction of the primary and secondary outcome, Student’s *t* tests will be performed for continuous variables and chi-square or Fisher’s exact test for categorical variables. Those variables in which statistically significant differences are found will be introduced in the analyses as covariates. Kaplan-Meier analysis with log-rank statistics will be used to assess event-free interval and Cox forward conditional proportional hazards for regression analysis. We plan intention-to-treat analysis of the primary outcome. The full analysis set and per-protocol set will be used for the assessment of efficacy. Interim analyses will be done annually for the first 5 years after index surgery, and the sample size would be adjusted accordingly. An interim analyses will be performed to see if the trial should be continued or stopped, and so it serves as a safeguard. If the outcomes are very poor, more than would be expected, a clear-cut trend towards increased severe morbidity (classed as Clavien-Dindo grade 3 or greater) in relation to either the control or test group, the trial would be stopped and the enrolled participants would have been followed for outcomes and the primary analysis would have focused on the mortality end point. Alternatively, if there was a clear difference between the two groups in terms of benefits for the test cohort, with statistically significant findings emerging on comparison of one group over another that support uncontestable differences between groups, then it might also be stopped and all enrolled participants will be followed for outcomes and the primary analysis will focus on the efficacy end point. Data will be monitored by the treating clinicians and external independent trial monitoring committee, and the principle investigator of each participative site will take overall responsibility. An external independent trial monitoring committee will also analyze interim anonymized outcome data. All analyses considered a *P* value of ≤ 0.05 as statistically significant.

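### Ending participation at surgical recurrence is an exit that depends on outcome and arm; it conflicts with the follow-up promised elsewhere and leaves later deaths unrecorded

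*Protocol article*

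**What the plan says.** All references are to the protocol article.

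- **Follow-up:** "If patients do develop surgical recurrence, their participation in the study is terminated". The reason given is that nothing further is left to observe once the main outcome has occurred. The same section keeps patients with endoscopic or clinical recurrence under observation until they need surgery. It schedules clinical, endoscopic and radiological review every six months, and asks for an unscheduled colonoscopy when symptoms suggest recurrence.
- **End points:** "In total, patients will be followed for 5 years after surgery". Endoscopic recurrence needs a Rutgeerts score of i2 or higher, and only disease "proximal to the anastomosis or in the perianastomotic area is considered to be consistent with endoscopic recurrence". Morbidity is limited to intra-operative and 30-day outcomes.
- **Statistical analysis:** after a stop for benefit, "all enrolled participants will be followed for outcomes". After a stop for harm, enrolled participants are likewise to be followed, and mortality becomes the subject of the primary analysis. Categorical outcomes are compared by chi-square or Fisher's test, and event-free intervals by Kaplan-Meier and log-rank.
- **Sample size:** "30% of subjects undergoing an ileocolonic anastomosis with conventional limited mesenteric excision would develop surgical recurrence at 60 months after surgery", and the effect is "To detect a 20% decrease in the surgical recurrence rate after wide mesenteric excision with 80% power and 5% significance".

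**The concern.** The rule makes leaving the study a consequence of the primary outcome. If the treatment works as hypothesised, more patients leave the limited-excision (LME) arm than the extensive-excision (EME) arm. This has two consequences.

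1. **Mortality.** Once a patient has left, later death is not recorded. If the trial stops for harm, the analysis that becomes primary would use vital status that is incomplete in a way related to both arm and disease severity.
2. **Endoscopic recurrence.** A patient who reaches reoperation without a prior i2 score has no endoscopic event. In a chi-square test that patient counts as event-free, and in a Kaplan-Meier analysis as censored, although the disease was bad enough to need surgery. The error runs towards no difference between the arms.

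**Working it through.** **Step 1. Which planning rates?** The control rate is 30%, and the stated decrease of 20% could be absolute (30% v 10%) or relative (30% v 24%). The plan's own total settles it: "with 80% power and 5% significance, a total of 100 patients must be recruited". The pooled two-proportion formula per arm is

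n = [z_α √(2p̄(1−p̄)) + z_β √(p₁(1−p₁) + p₂(1−p₂))]² / (p₁−p₂)²

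- 30% v 10%, one-sided 5%: (1.645 × 0.5657 + 0.8416 × 0.5477)² / 0.04 = 48.4, so 49 per arm and 98 in total. This is within 2 of the stated 100.
- 30% v 10%, two-sided 5%: 62 per arm, 124 in total.
- 30% v 24%: 1,352 in total one-sided, 1,718 two-sided.

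Only the absolute reading is compatible with a total near 100. (That the match needs a one-sided test is a separate matter.)

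**Step 2. How many patients leave?** The allocation ratio is not stated. Assuming 1:1, 116 gives 58 per arm.

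- LME: 58 × 0.30 = 17.4
- EME: 58 × 0.10 = 5.8
- Total 23.2, or 20% of 116; ratio 3.0

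**Step 3. How much follow-up time is lost?** Assume a constant hazard λ = −ln(1−p)/5. The mean time observed over five years is p/λ.

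- LME: λ = 0.0713, observed 4.21 years, lost 0.79 years (15.9%)
- EME: λ = 0.0211, observed 4.75 years, lost 0.25 years (5.1%)

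The Cessation of trial section stops the trial five years after first enrolment. With uniform accrual over the stated enrolment period (an assumption), the figures become 14.5 v 4.7 patients and 13.3% v 4.2% of follow-up time. The ratio stays near 3.

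**Step 4. Effect on mortality.** The documents give no death rate, so the number of missed deaths cannot be computed. What can be said is that the time in which a death would be missed is about three times as long in the LME arm.

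**Step 5. Effect on endoscopic recurrence.** Let f be the fraction of reoperated patients with no earlier i2 score, taken as equal in both arms. The observed difference shrinks by f × (0.30 − 0.10), that is f × 20 percentage points. The documents do not give f. For scale only, assume true recurrence of 65% v 40%, also not in the documents. The observed rates are then 0.65 − 0.30f and 0.40 − 0.10f. Two-sided 5% power with 58 per arm is:

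| f | LME / EME patients affected | Observed difference | Power |
|---|---|---|---|
| 0 | 0 / 0 | 25 points | 78% |
| 5% | 0.9 / 0.3 | 24 points | 74% |
| 10% | 1.7 / 0.6 | 23 points | 70% |
| 20% | 3.5 / 1.2 | 21 points | 62% |

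The colonoscopy schedule in the Follow-up section points to the upper rows.

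**The case against.** The case against runs as follows.

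- **The statements can be read together.** Five years in total may mean a maximum, and the promise quoted from the Statistical analysis section covers only a stop for benefit, where following each patient to surgical recurrence would suffice. This stands in part. It does not answer the harm-stop sentence, which needs deaths among all enrolled patients, including those already reoperated.
- **The endoscopic loss does not come from the exit.** Keeping a reoperated patient enrolled would not supply a score for an anastomosis that has been removed. What matters is how reoperation is counted, and that is often left to the analysis plan. This stands as to cause. The remedy is still one clause, and it belongs beside the sentence that has to change anyway.
- **Few patients are affected.** With review every six months and colonoscopy for symptoms, most reoperated patients should already have an i2 score, and data collected before exit are kept. This stands.

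A reader might infer more, and the documents do not support it:

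- *That the worst patients vanish from the endoscopic data, with a large loss of power.* Anyone already scored i2 or higher is counted. At f = 50% the power in the model above would fall to 37%, but that needs about 9 of 17 LME patients to reach surgery unscored, which the colonoscopy schedule makes implausible.
- *That planned reoperation-morbidity data are lost.* Morbidity of a later operation is not a listed end point.
- *That the primary result is biased.* Time to first surgical recurrence is complete at the event. Bias would need the site's classification of a reoperation to be overturned later, and nothing in the article describes that.

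**Conclusion.** The point holds in limited form. The Follow-up rule conflicts with the Statistical analysis section and sits badly with the five-year statement under End points. The exit it creates depends on outcome and arm: about 17 v 6 patients, assuming the planning rates and 1:1 allocation. Its definite cost is unequal loss of vital status after reoperation. That matters if the harm-stop analysis is ever run, and its size is unknown. Its lesser cost is a bias of f × 20 points towards no difference in endoscopic recurrence, probably about one or two points. That estimate rests on judging f to be small (5% to 10%), since the article gives no value. The primary analysis stands as planned. This is a cheap improvement, not a flaw that threatens the trial's main conclusion.

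**What to change.** Reconcile the End points, Follow-up and Statistical analysis sections by replacing the sentence on termination with three statements:

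1. Surgical recurrence completes the primary end point and ends scheduled study endoscopy, but it does not end participation.
2. Vital status and any further Crohn's surgery are recorded to 60 months from the index operation, from hospital records or by telephone.
3. In the endoscopic-recurrence analysis, surgical recurrence counts as an event on the date of surgery if no endoscopic recurrence was recorded before.

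The cost is a short record for about 23 patients (17.4 + 5.8 at the planning rates). The trade-off is that the secondary end point becomes endoscopic or surgical recurrence and should be labelled so. No extra endoscopy is needed and patient management does not change.
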